### Setting and Duration

The current study will consecutively enroll patients diagnosed with different types and stages of solid organ malignant tumors who are candidates for treatment with ICIs. In the setting of outpatient clinics, patients will be recruited by the medical oncologists responsible for their care in one of the participating hospitals. Recruitment will continue until the desired sample size is reached (see “*Study size calculation*” section). The autoantibody panel under study will be performed when the whole cohort reaches week 48 of follow-up from the time of inclusion, which will coincide with the ICI initiation date. Patients lost to follow-up will be censored at the time of their last follow-up.

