### Participants

All patients diagnosed with a solid organ malignant tumour of any stage amenable to ICI therapy according to current guidelines are potentially eligible to participate. Patients will be included by the medical oncologists in charge in the outpatient clinic setting.

The patients must meet all the following inclusion criteria:1) Initiation of treatment with an ICI or a combination of ICIs2) ICI naïve status, though those treated in the past with other systemic therapies for cancer, such as chemotherapy or tyrosine-kinase inhibitors, may be included3) Provision of written informed consent.

Exclusion criteria will be the following:1) Life expectancy of less than 3 months from the start of ICI therapy2) Contraindication to ICI therapy: proven hypersensitivity or history of anaphylactic allergic reactions secondary to ICIs, active severe autoimmune disease, or poor performance status (Eastern Cooperative Oncology Group score ≥ 3)3) Active immunosuppressive treatment: prednisone at doses >10 mg/day or equivalent (e.g., 1.5 mg/day of dexamethasone), azathioprine, methotrexate, mycophenolate, cyclophosphamide, rituximab, leflunomide, anti-tumor necrosis factor agents (infliximab, etanercept, adalimumab, golimumab), or abatacept, among others.

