Data related to the tumour:• Tumour type• Date of diagnosis• PD-L1 expression in tumour cells (%)• Date of initiation of ICI therapy• Dates of ICI administration• Date of progression• Date of death• Progression-free survival, defined as time from start of ICI therapy to tumor progression, death or last day of follow-up• Overall survival, defined as time from start of ICI therapy to death or the last day of follow-up• Cause of death: cancer-related, non-cancer-related, ICI-associated toxicity (immune-related, non-immune-related adverse event, infection or other).

Data related to treatment received before ICI initiation:• Nonsteroidal anti-inflammatory drugs• Glucocorticoids• Other immunomodulatory drugs: e.g., colchicine, hydroxychloroquine, mesalazine, or sulfasalazine• Oral anticoagulants (acenocoumarol, low-molecular-weight heparin, direct oral anticoagulants).

Data related to ICI:• Type: anti-CTLA4 (ipilimumab), anti-PD1 (nivolumab and pembrolizumab), anti-PD-L1 (atezolizumab, avelumab, and durvalumab)• Monotherapy or combination therapy (description)• Adjuvant or palliative therapy, and if palliative, line of therapy (first line, second line, other).

Laboratory data:

Obtained from blood samples for care and research purposes:• Glomerular filtration rate (ml/min/m^2^), levels of glucose (mg/dl), bilirubin (mg/dl), alanine aminotransferase, aspartate aminotransferase, gamma-glutamyltransferase (U/L), and thyroid stimulating hormone (μUI/mL).• Prothrombin time (percentage) or international normalized ratio (INR)• Complete cell count: haemoglobin (g/dl), white blood cells (/µL), differential white blood cell count of neutrophils, lymphocytes, monocytes, and eosinophils (/μL) and platelets (/μL)• Lipid profile: levels of cholesterol, triglycerides, and high- and low-density lipoprotein cholesterol (mg/dl).

Obtained from blood samples only for research purposes:• 25-hydroxycholecalciferol (ng/ml) at weeks 0, 24 and 48.• Levels of the autoantibodies under study (i.e., ANAs, RF and ANCAs) in ordinary samples according to study schedules (Figures 1, 2) and extraordinary samples.

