### Sample Size Calculation and Statistical Analysis

To estimate an expected sensitivity of the autoantibody panel under study of 0.90 with a 95% confidence interval of not less than 0.75, 70 cases with irAEs will be needed. Considering irAEs associated with ICIs will develop in 25% of cases (Wang et al., 2019), a total of 210 patients without irAEs will be required. Considering a loss to follow-up of 5%, we should recruit a total of 294 patients.

Regarding the statistical analysis, firstly, a description of the cohort will be performed. Quantitative variables will be reported as mean ± standard deviation or median (interquartile range) and compared between groups using Student’s t-test for unpaired data or the Mann-Whitney U-test, depending on whether data follow a normal distribution. Categorical variables will be expressed as frequencies (percentages) and compared between groups using Pearson’s Χ^2^ or Fisher’s exact test based on the expected frequency of cells. To assess the primary endpoint of the study (i.e., proportion of patients developing at least an irAE), the autoantibody panel will be considered positive when any of the autoantibodies included in the panel is positive according to the following cut-off points: ANA titers ≥ 1:40, ANCA titers ≥ 1:20 or RF value ≥ 30 IU/ml. The autoantibody panel and the titers of autoantibodies will be handled as a categorical variable (namely, positive or negative result) and as a quantitative variable, respectively. It is planned to perform a subgroup analysis depending on whether or not patients have an AD before their inclusion. An analysis of variance for repeated measures will be performed to explore the profile of detectable autoantibodies over the 48 weeks of follow-up.

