Survival will be assessed using a Kaplan-Meier analysis and compared between groups using the log-rank Mantel-Cox test. A subgroup analysis according to tumour type and extent of cancer (local, advanced, and metastatic disease) will be performed to assess survival outcomes*.* A multivariate analysis using logistic regression and Cox regression will be performed to detect factors associated with the occurrence of irAEs. Applying a manual backward stepwise procedure, a multivariate model will be constructed from variables that either have a p-value of less than 0.10 in the univariate analysis or are considered relevant to the dependent variable on the basis of previous studies (e.g., sex and age of patients, type of ICI). Variables not reaching statistical significance will be dropped from the final predictive model. The sensitivity, specificity, positive predictive value, negative predictive value, and probability ratios with their corresponding 95% confidence intervals of the model will be calculated. The diagnostic accuracy of the predictive model inferred from the logistic regression model will be described with the area under the receiver operating characteristic curve.

Two-sided hypothesis tests will be performed, and the significance level will be set at 5%. The statistical analysis will be conducted using IBM SPSS Statistics software version 27.0 (Chicago, IL).

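### Survival is to be analysed by extent of cancer, which is not among the listed variables, and the comparison of survival with and without irAEs takes no account of it

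*Protocol article*

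**What the plan says.** Eligibility is broad. Under Participants: "All patients diagnosed with a solid organ malignant tumour of any stage amenable to ICI therapy according to current guidelines are potentially eligible". Setting and Duration likewise describes "patients diagnosed with different types and stages of solid organ malignant tumors who are candidates for treatment with ICIs".

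The analysis section (Sample Size Calculation and Statistical Analysis) commits to the following: "A subgroup analysis according to tumour type and extent of cancer (local, advanced, and metastatic disease) will be performed to assess survival outcomes". It does not define the three categories, and it does not say whether extent is taken at diagnosis or at ICI start.

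The Variables section itemises what is collected. The tumour block begins "Data related to the tumour:• Tumour type• Date of diagnosis• PD-L1 expression in tumour cells (%)• Date of initiation of ICI therapy" and goes on to dates of ICI administration, progression and death, the definitions of progression-free and overall survival, and cause of death. It has no item for stage, TNM or extent. The ICI block does include "Adjuvant or palliative therapy, and if palliative, line of therapy (first line, second line, other".

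Secondary Objectives includes a comparison of cancer-related survival between patients who develop irAEs and those who do not. The analysis section gives Kaplan-Meier with the log-rank test for survival. It states logistic and Cox regression for factors associated with the occurrence of irAEs, not for survival. Management of Confounding and Interaction Factors deals with glucocorticoids, pre-existing autoimmune disease and sex, and does not mention extent.

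**The concern.** There are two linked problems.

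First, a named analysis variable does not appear in the list of collected variables. That list is otherwise detailed, down to laboratory units and individual anticoagulants, so two stated parts of the same document disagree.

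Second, and more important for inference, extent of disease plausibly acts on both sides of the irAE survival comparison. Patients with less extensive disease can be expected to live longer. They may also stay on ICI longer and so have more opportunity for an irAE. If so, patients with irAEs would appear to survive longer even where the irAE has no bearing on survival. A log-rank test over the whole cohort does not remove this, and the only stated analysis that would expose it is the subgroup analysis whose defining variable is unlisted.

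**Working it through.** **Plan's own figures.** The article gives no figure on this point. Its sample size is not in dispute: 70 irAE cases at 25% give 70 / 0.25 = 280 patients, of whom 280 − 70 = 210 have no irAE, and 280 × 1.05 = 294. Adding an extent variable changes none of these.

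**Does any listed item supply extent?**

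| Level needed | What the listed items give |
|---|---|
| Local | Adjuvant therapy is a partial proxy, not an exact match |
| Advanced | Palliative, with line; not separable from metastatic |
| Metastatic | Palliative, with line; not separable from advanced |

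Tumour type is listed, so that half of the planned subgroup analysis is supported.

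**How large could the case-mix effect be?** Every input in this part is an assumption; the article gives none of them by extent. Suppose the cohort has two groups with shares w1 and w2, irAE risks r1 and r2, and 48-week mortality m1 and m2. Mortality within each group is the same with or without an irAE, so the true irAE effect is zero. All deaths are treated as cancer-related. Then:

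- mortality with irAE = (w1·r1·m1 + w2·r2·m2) / (w1·r1 + w2·r2)
- mortality without irAE = (w1·(1−r1)·m1 + w2·(1−r2)·m2) / (w1·(1−r1) + w2·(1−r2))

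*Scenario A, adjuvant against metastatic.* Half in each group; mortality 5% and 45%; irAE 35% and 15%, which average to the 25% used for the sample size.
- With irAE: (0.175 × 0.05 + 0.075 × 0.45) / 0.25 = 0.0425 / 0.25 = 17.0%
- Without: (0.325 × 0.05 + 0.425 × 0.45) / 0.75 = 0.2075 / 0.75 = 27.7%
- Apparent benefit: 10.7 points

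*Scenario B, as A with irAE risks of 30% and 20%* (still 25% overall).
- With irAE: (0.15 × 0.05 + 0.10 × 0.45) / 0.25 = 0.0525 / 0.25 = 21.0%
- Without: (0.35 × 0.05 + 0.40 × 0.45) / 0.75 = 0.1975 / 0.75 = 26.3%
- Apparent benefit: 5.3 points

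*Scenario C, as A with an adjuvant share of 10%* (overall irAE risk then 17%).
- With irAE: (0.035 × 0.05 + 0.135 × 0.45) / 0.17 = 0.0625 / 0.17 = 36.8%
- Without: (0.065 × 0.05 + 0.765 × 0.45) / 0.83 = 0.3475 / 0.83 = 41.9%
- Apparent benefit: 5.1 points

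A to C contrast adjuvant with metastatic patients, a contrast that the listed treatment-intent item could largely remove if the analysis used it. The gap left by the list is within palliative patients.

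*Scenario D, palliative patients only.* Half locally advanced (mortality 15%, irAE 30%) and half metastatic (45%, 20%).
- With irAE: (0.15 × 0.15 + 0.10 × 0.45) / 0.25 = 0.0675 / 0.25 = 27.0%
- Without: (0.35 × 0.15 + 0.40 × 0.45) / 0.75 = 0.2325 / 0.75 = 31.0%
- Apparent benefit: 4.0 points, which splitting by treatment intent would not remove

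In all four scenarios a comparison made within levels of extent gives a difference of zero, which is the truth by construction.

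**The case against.** The strongest reply is that this is a journal article condensing a full protocol. The case report form is not shown, the analysis section itself names the variable and its levels, and the treating oncologists who enrol patients know the stage. That stands in part. A reader might infer that the subgroup analysis cannot be run; the document does not show this. It shows only that the analysis cannot be run from the variables listed. If the missing item were the whole point, it would be a minor comment.

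A reader might also infer that adjuvant and metastatic patients remain mixed. The listed treatment-intent and line item contradicts that: adjuvant patients can be separated from palliative ones, and the item is also among the candidate irAE predictors. What remains is that no stated survival comparison uses it, and that it cannot split advanced from metastatic disease.

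The third objection is to the size. The 11-point figure comes from one chosen scenario and falls to about 5 points under milder inputs. This is correct, and the figures should be read as a range of illustrations rather than an estimate.

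Finally, the choice between subgroup, stratified and adjusted analyses is often left to a statistical analysis plan. But the article does state its survival method, without adjustment, and reserves its regression for another outcome. Separate subgroup results would show the pattern by extent, but they do not yield one comparison of patients with and without irAEs that is free of case mix.

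**Conclusion.** The point holds in a limited form. Extent of cancer defines a planned survival subgroup but is absent from the listed variables, and the listed treatment-intent item is only a partial substitute. As specified, the comparison of cancer-related survival by irAE status is open to confounding by extent in a cohort of any stage.

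Under the assumed inputs the spurious difference in 48-week mortality is roughly 5 to 11 points when treatment intent is ignored as well, and about 4 points within palliative patients in one scenario. Its direction rests on the assumption that less extensive disease carries both lower mortality and more irAEs.

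It would be tempting to say that all four key secondary survival endpoints are biased. The document does not support that. The irAE against no-irAE comparison is set for cancer-related survival; irAE-free survival is compared by autoantibody status; and no comparison by irAE status is stated for progression-free or overall survival. The primary endpoint, the diagnostic accuracy objective and the sample size are not touched.

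**What to change.** 1. Add extent of disease at ICI start to the tumour data under Variables, as local, locally advanced or metastatic, with a definition of each level. For patients already enrolled, take it from the oncology record.
2. Make the comparison of cancer-related survival with and without irAEs stratified by extent, either by a stratified log-rank test or by Cox regression with extent as a stratum or covariate. Keep the planned subgroups alongside it.

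The cost is one data field and one model term, with no added visits, samples or patients. Some strata may be sparse. With about 70 irAE cases expected, an even split over three levels would leave about 23 in each (70 / 3), and an uneven split fewer in some. If a level is too thin to serve as a stratum, extent can enter the Cox model as a covariate instead.

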### Side Effects of Immune Checkpoint Inhibitor Therapy: Immune-Related Adverse Events and Possible Predisposing Factors

By unblocking certain immune regulatory mechanisms, ICIs can exacerbate pre-existing autoimmune diseases (ADs) (Abdel-Wahab et al., 2018), whose prevalence is estimated to be between 3 and 8% in the general population (Davidson and Diamond, 2001; Cooper and Stroehla, 2003; Tobón et al., 2012), or induce *de novo* immune-related adverse events (irAEs) (De Velasco et al., 2017; Postow et al., 2018). Descriptions have been published of a wide variety of irAEs, both organ-specific (hypophysitis, colitis, pneumonitis, encephalitis, thyroiditis, dermatitis-rash, vitiligo, arthritis, hepatitis, myasthenia gravis) and systemic [Sjögren’s syndrome, giant cell arteritis, systemic lupus erythematosus (SLE), remitting seronegative symmetrical synovitis with pitting edema (RS3PE) syndrome, polymyalgia rheumatica, systemic vasculitis, antiphospholipid syndrome], which hamper treatment in a significant percentage of patients with an established indication for ICIs (Spain et al., 2016). On the other hand, patients with a history of ADs, some of which are considered risk factors for cancer (Trallero-Araguás et al., 2012; Bernal-Bello et al., 2017; Lazzaroni et al., 2017; Yang et al., 2017), have been systematically excluded from pivotal clinical trials on ICIs (Haanen et al., 2020). Thus, experience with the use of ICIs in patients with ADs is scarce and comes from post-marketing observational studies (Johnson et al., 2016; Donia et al., 2017; Menzies et al., 2017; Tang et al., 2021). Despite this barrier to patients with ADs accessing treatment with ICIs, several studies suggest that the response rate is higher in patients with irAEs than those without irAEs (Attia et al., 2005; Teulings et al., 2015; Judd et al., 2017; Fujii et al., 2018; Kostine et al., 2018; Maher et al., 2019; Hussaini et al., 2021). In contrast, immunosuppressive treatment aimed at controlling irAEs may reduce the anti-tumor effect of ICIs, by “immune dampening” (Weber et al., 2016; Kim et al., 2017; Bai et al., 2021). Overall, there is a need for better clinical and immunological characterization of patients who develop irAEs.

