### Summary

We are currently witnessing an exponential increase in publications on irAEs; most of them focus, however, on identifying predictors of efficacy rather than toxicity (Hopkins et al., 2017). Nevertheless, recent years have seen the emergence of several methods seeking to achieve early detection of irAEs (Patil et al., 2018; Nakamura, 2019; von Itzstein et al., 2020), namely, analysis of lymphocyte subpopulations (Das et al., 2018), autoantigen microarrays (Gowen et al., 2018; Tahir et al., 2019), molecular omics data (Jing et al., 2020), gene signatures and polymorphisms (Friedlander et al., 2018; Abdel-Wahab et al., 2021), and the gut microbiome (Dubin et al., 2016). All these still experimental tools share the drawback of a high level of complexity, limited availability, and high cost. In parallel, other more accessible risk factors and markers have been suggested, namely, female sex (Valpione et al., 2018), total white blood cell and lymphocyte counts (Fujisawa et al., 2017), peripheral eosinophilia (Chu et al., 2020), sarcopenia (Daly et al., 2017), vitamin D deficiency (Bersanelli et al., 2017) and levels of more easily measurable interleukins (ILs) such as IL-6, IL-17 and IL-10 (Sun et al., 2008; Tarhini et al., 2015). Overall, there is a need for better clinical and immunological characterization of patients who develop irAEs, especially those with pre-existing ADs. Despite systematization efforts (Haanen et al., 2018; Schneider et al., 2021), it remains unclear how best to manage irAEs, and to tackle this question, there is a need to thoroughly understand the duality between the anti-tumor and the immunogenic effects of ICIs.

For all these reasons, the AUTENTIC study aims to investigate the usefulness of a sensitive, accessible, and inexpensive panel of autoantibodies, consisting of ANAs, RF, and ANCAs, to detect patients at risk of developing irAEs induced by ICIs. We also aim to describe the autoantibody profile, the potential early appearance or aggregation of autoantibodies over time, and the impact of irAEs on cancer-related survival of patients receiving ICIs.

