#### Secondary Objectives

• To describe the profile of detectable autoantibodies over a 48-weeks follow-up in patients with cancer treated with ICIs, regardless of whether they develop irAEs• To compare irAE-free survival among patients positive for autoantibodies before ICI initiation, patients positive for autoantibodies after ICI initiation and patients negative for autoantibodies throughout follow-up• To analyze cancer-related survival in patients treated with ICIs who develop irAEs and compare it with that in patients who do not develop irAEs• To investigate the potential early appearance and/or aggregation of autoantibodies over time up to the time of irAEs diagnosis.

This study protocol corresponds to the first phase of the AUTENTIC project, which will be followed by an external validation of a predictive model of irAEs with prospective data in an independent cohort of patients.

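### The comparison of cancer-related survival with and without irAEs takes no account of ICI regimen or line of therapy, so these may confound it

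*Protocol article*

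**What the plan says.** Secondary Objectives sets the comparison: "To analyze cancer-related survival in patients treated with ICIs who develop irAEs and compare it with that in patients who do not develop irAEs". The Summary of the Introduction lists, among the things the study aims to describe, "the impact of irAEs on cancer-related survival of patients receiving ICIs".

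The method is in Sample Size Calculation and Statistical Analysis: "Survival will be assessed using a Kaplan-Meier analysis and compared between groups using the log-rank Mantel-Cox test". The next sentence adds the only other factors given for survival: "A subgroup analysis according to tumour type and extent of cancer (local, advanced, and metastatic disease) will be performed to assess survival outcomes".

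The regression models follow, and their purpose is stated: "A multivariate analysis using logistic regression and Cox regression will be performed to detect factors associated with the occurrence of irAEs". Type of ICI appears only as a candidate for that model, among variables "considered relevant to the dependent variable on the basis of previous studies (e.g., sex and age of patients, type of ICI").

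The cohort is mixed. Participants admits patients starting one ICI or a combination, with a solid tumour of any stage. Variables records the regimen and setting: "Monotherapy or combination therapy (description)• Adjuvant or palliative therapy, and if palliative, line of therapy (first line, second line, other").

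**The concern.** Here irAE status is the exposure and survival is the outcome. A baseline factor that affects both confounds the comparison. ICI regimen is a candidate. The analysis section treats type of ICI as relevant to irAE occurrence, and the Discussion says that growing use of combinations spreads irAEs to more patients. It is plausible that regimen and line of therapy also relate to survival, because they follow the indication and the stage of the disease.

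If so, patients with irAEs will differ from the others in regimen mix, and part of any survival difference will belong to the regimen. An unadjusted log-rank test cannot separate the two. The protocol uses type of ICI when irAE is the outcome and gives it no role when irAE becomes the exposure.

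**Working it through.** **Text check.** The factors given a role in each analysis are:

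| Analysis | Method | Factors named |
|---|---|---|
| irAE occurrence | logistic and Cox regression, backward selection | sex, age, type of ICI, others by p-value |
| Survival | Kaplan-Meier, log-rank | subgroups by tumour type and extent |

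Management of Confounding and Interaction Factors adds only glucocorticoids given for reasons other than an irAE, handled in the multivariate analysis. Nothing assigns regimen or line to the survival comparison.

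**Size.** The protocol states no figure for the survival comparison, so there is none to reproduce. One input comes from the protocol, the overall irAE risk of 25% (70 cases and 210 non-cases, 280 in all). The rest are assumptions:

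- share on combination, pc = 0.20 to 0.30
- irAE risk on combination = 0.45
- survival hazard ratio for combination versus monotherapy, h = 0.5 to 0.7
- no true effect of irAEs on survival

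Combination share in each group:

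- with irAE: a = pc × 0.45/0.25, which gives 0.36 (pc = 0.20) or 0.54 (pc = 0.30)
- without irAE: b = pc × 0.55/0.75, which gives 0.147 or 0.22

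The apparent hazard ratio, approximated as the ratio of mean hazards, is (1 − a(1 − h)) / (1 − b(1 − h)):

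| pc | h = 0.5 | h = 0.7 |
|---|---|---|
| 0.20 | 0.820/0.927 = 0.885 | 0.892/0.956 = 0.933 |
| 0.30 | 0.730/0.890 = 0.820 | 0.838/0.934 = 0.897 |

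The range is 0.82 to 0.93 with no true irAE effect.

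**Second set of assumptions.** Take 48-week survival of 0.60 on monotherapy, combination shares of 20-50% with irAE and 10-15% without, and h = 0.6 to 0.8. The ratio of cumulative hazards at week 48 is then about 0.85 to 0.98. At h = 0.6, for example, survival on combination is 0.60^0.6 = 0.736. Shares of 0.50 and 0.15 give group survival of 0.668 and 0.620, and ln(0.668)/ln(0.620) = 0.845.

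**Direction.** If combination patients had the worse prognosis, the sign would reverse. With the inverse hazard ratios, h = 1/0.7 = 1.43 and 1/0.5 = 2, the same formula gives:

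- pc = 0.20, h = 1.43: 1.154/1.063 = 1.09
- pc = 0.30, h = 2: 1.54/1.22 = 1.26

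**Against sampling error.** Assume 30-50% of 280 patients die (84 to 140 deaths) and 25% have irAEs. The standard error of the log hazard ratio is 1/√(D × 0.25 × 0.75), which is 0.25 to 0.20. The log of 0.93 to 0.82 is −0.07 to −0.20, so the bias is at most about one standard error.

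**The case against.** Several points on the other side have force.

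- **The planned subgroups cover part of it.** Extent of disease is close to adjuvant versus palliative use, and regimen probably goes with tumour type. This stands in part: the figures above are for the pooled cohort and would be smaller within those subgroups. But combination use and line can still vary within a tumour type and stage, and subgroups do not give an adjusted overall comparison.
- **The link from regimen to survival is thinly documented.** The Discussion cites a benefit of one combination in melanoma, and one of its two drugs is not among the ICI types listed under Variables. This stands, so size and direction remain assumptions.
- **The aim is secondary and introduced as descriptive.** This stands and limits the severity. A reader might infer that the survival question cannot be answered at all, which is too strong for a descriptive comparison.
- **An analysis plan that is not shown might add covariates.** It might, but the article names the test, the subgroup factors and the purpose of the regressions. The point concerns what is stated.

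A reader might also infer that ignoring immunosuppression given for irAEs is an error, since the Introduction says that "immunosuppressive treatment aimed at controlling irAEs may reduce the anti-tumor effect of ICIs". The documents do not support that. This treatment follows the irAE and is given only to patients who have one, so it is a consequence of the exposure and not a confounder. If it offset a benefit, the result would be a true net result for irAEs as managed. The objective does not ask for an effect net of treatment.

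**Conclusion.** The concern holds for ICI regimen and line of therapy. As written, the comparison is unadjusted for baseline factors that vary across the cohort, and the protocol itself links type of ICI to irAE risk. Confounding is possible but not demonstrated, and neither its size nor its direction can be derived from the documents. The 0.82 to 0.93 rests entirely on the assumed combination share, irAE risk and hazard ratio. It is modest beside the likely sampling error. The primary objectives are unaffected.

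The concern does not extend to immunosuppression for irAEs, which is no error in the plan. The timing of irAEs is a separate matter: irAE status arises after ICI start and needs its own handling, which adjustment for regimen would not supply.

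**What to change.** In Sample Size Calculation and Statistical Analysis, state that the survival comparison between patients with and without irAEs uses a log-rank test or Cox model stratified by, or adjusted for, ICI regimen (monotherapy or combination) and treatment setting (adjuvant, first line, later line). Keep the subgroups by tumour type and extent. Describe the comparison as one of irAEs as managed. A split by immunosuppression is optional and, if shown, should be labelled descriptive because it also reflects irAE severity. Handle irAE timing separately.

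The cost is wording only, since the variables are already collected. Intervals will be slightly wider. Two regimens by three settings make six strata, about 47 of the 280 patients each on average (280/6). Some may be sparse, in which case covariate adjustment is the easier form.
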